### Postoperative radiotherapy

Adjuvant WBI with 3D conformal radiation therapy or intensity-modulated radiation therapy to the remaining breast is mandatory after BCS. The radiotherapy target area will not include the axillary region, and chest wall irradiation can be omitted with mastectomy. In this trial, either conventional fractionated radiotherapy or macrofractionated radiotherapy regimens will be used. The conventional fractionated whole breast radiotherapy dose will be 50 Grey (Gy) in 25 fractions, with a single dose of 2.0 Gy, five times per week. The tumour bed area will be selected to be added simultaneously or sequentially to DT60 Gy in 25 fractions, with a single dose of 2.4 Gy in fraction. The macro-fractionated radiotherapy whole breast radiotherapy dose will be 43.5 Gy in 15 fractions with a single dose of 2.9 Gy. The tumour bed area will be increased to 52.5 Gy in 18 fractions with a single dose of 2.9 Gy.

### Adjuvant systemic treatment

Systemic adjuvant therapies will be administered in accordance with local and international guidelines, including adjuvant chemotherapy, targeted therapy, endocrine therapy and immunotherapy are administered in accordance with nationally approved product information. Postoperative adjuvant therapy is required for HER2-positive or triple-negative breast cancer, regardless of ALN status. For HR+/HER2–, genetic testing may be used to guide decisions regarding adjuvant chemotherapy.

### Endpoints

#### Primary endpoint

The primary endpoint of this trial is 3 year invasive disease-free survival (iDFS), defined as the time from surgery to local recurrence, regional recurrence, distant metastasis, infiltration of the contralateral breast cancer or death from any cause, whichever occurs first.

#### Secondary endpoints

BCRL incidence: two measurements will be used to diagnose BCRL, and BCRL is diagnosed by meeting one of them.

##### 1. Relative volume change (RVC) of >10% in the affected upper limb

The upper limb volume will be calculated using the method of multisegmental arm circumference measurement. Five points will be taken to measure arm circumference. The midpoint of the ulnar styloid process at the distal end of the arm will be the starting point and measurements will be taken every 10 cm from this point towards the proximal end of the arm up to 40 cm. These five measurement points enable the limb to be divided into four truncated cones. The volume of each limb segment is calculated using the following formula:

V=[h (C12+C22+C1C2)]/12π

where C1 and C2 denote the arm circumference at the upper and lower points of the measurement segment, h=10 cm. The volume of the entire upper limb is the sum of the volumes of the segments. RVC is calculated using the following formula^32^:

RVC=[(A2×U1])/(U2×A1)]−1

where A1 indicates the volume of the affected upper limb at baseline, A2 indicates the volume of the affected upper limb at a specific time point, U1 represents the volume of the unaffected upper limb at baseline and U2 indicates the volume of the unaffected upper limb at a specific time point. The incidence of BCRL will be assessed at each follow-up timepoint.

##### 2. Bioelectrical impedance analysis (BIA)

The single-frequency bioimpedance analysis (SFBIA) ratio is defined as the ratio of the unaffected to the affected side.^33^ The SFBIA ratio of both upper limbs at 1 kHz and 5 kHz will be measured using bioelectrical impedance technology. The diagnostic criteria in this study will refer to the findings of Liu Miao *et al*. BCRL recognition is superior when the threshold is set at the mean+2 SD for healthy women.^34^ BCRL will be diagnosed when any one of the following is fulfilled:

The dominant affected arm SFBIA ratio at 1 kHz of >1.067.The nondominant affected arm SFBIA ratio at 1 kHz of >1.043.The dominant affected arm SFBIA ratio at 5 kHz of >1.068.The nondominant affected arm SFBIA ratio at 5 kHz of >1.044.PROs: Patients will be followed up with questionnaires using FACT-B (Version 4.0) and Quick DASH during the same period as the BCRL assessment. The FACT-B scale will be used to assess changes in QoL in breast cancer patients with SLNB omission from baseline to 3 years after surgery. The Quick DASH scale will be used to assess changes in arm morbidity from baseline to 3 years after surgery.Locoregional recurrence (LRR), local recurrence (LR), regional recurrence (RR)： LR is defined as the time from surgery to the appearance of a tumour in the ipsilateral breast, chest wall or skin at the surgical scar. RR is defined as the time from surgery to the appearance of a tumour in the lymphatic drainage area of the affected side, including the axillary, supraclavicular, subclavicular and internal mammary lymph node regions. Clinical recurrence suggested by imaging or other investigations requires a definitive diagnosis by cytology or histopathology. Suspected recurrent lesions for which histological or cytological examination is not possible will be submitted to the Data Safety Monitoring Board (DSMB) for independent review.

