Although SLNB is a minimally invasive surgical procedure for axillary staging, it is still associated with adverse sequelae. In the ACOSOG Z0011 trial,^13^ approximately one-quarter of the patients in the SLNB group had postoperative complications (including wound infection, lymphedema, axillary sensory abnormalities and brachial plexus injury), and lymphoedema was present in 8% of the patients 6 months after SLNB. The incidence of sensory neuropathy in the SLNB group in the IBCSG 23–01 trial was as high as 13%,^14^ whereas the incidence of lymphoedema was 4%. Similarly, the ALMANAC trial reported a 7% incidence of lymphoedema in the SLNB group.^3^ Considering that SLNB is nontherapeutic and primarily performed for axillary staging, SLNB may represent an overtreatment for SLN-negative patients, and omitting SLNB may result in improved QoL.

In recent years, there have been significant improvements in the accuracy of imaging modalities for preoperative noninvasive axillary staging. A combination of imaging techniques is superior to a single imaging technique for the evaluation of axillary lymph node (ALN) status.^21^ Ultrasonography is the method of choice for ALN assessment in patients with breast cancer.^22^ Choi *et al* found that the specificity of ultrasound assessment of nonpalpable metastatic lymph nodes was 88%–98%.^23^ Another recent meta-analysis revealed that [18F]-fluorodeoxyglucose positron emission/magnetic resonance imaging (FDG PET/MRI) had a higher diagnostic performance compared with MRI in detecting ALN metastases,^24^ but another study found no statistically significant difference between PET/MRI and MRI for N stages.^25^ Preliminary data suggest that PET/MRI has the potential to improve the diagnostic performance of ALN staging, but further studies are needed to confirm and expand the current evidence. Although axillary surgery reduces the risk of axillary recurrence through the local control of the axilla, systemic adjuvant therapy and axillary radiotherapy are also effective. Moreover, postoperative adjuvant therapy should be considered based on the biological characteristics of the tumour rather than the number of ALN involved. Breast cancer treatment decisions frequently rely on tumour biology and genetic profiles. Therefore, the assessment of ALN status is becoming less important.

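### The bioimpedance criteria for lymphoedema are absolute cut-offs with no baseline condition, so arm asymmetry present before surgery counts as incident BCRL

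*Protocol article*

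**What the plan says.** Under Secondary endpoints, the protocol article gives two routes to the diagnosis: "two measurements will be used to diagnose BCRL, and BCRL is diagnosed by meeting one of them".

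- **Relative volume change (RVC) above 10%.** The RVC formula divides by the baseline volumes of both arms, so it is corrected to the patient's own starting point.
- **Bioelectrical impedance analysis (BIA).** The single-frequency (SFBIA) ratio of unaffected to affected side is read at 1 kHz and 5 kHz. The rationale is "BCRL recognition is superior when the threshold is set at the mean+2 SD for healthy women", and the rule is "BCRL will be diagnosed when any one of the following is fulfilled". For the dominant arm the criteria are "The dominant affected arm SFBIA ratio at 1 kHz of >1.067" and "The dominant affected arm SFBIA ratio at 5 kHz of >1.068". For the nondominant arm they are "The nondominant affected arm SFBIA ratio at 1 kHz of >1.043" and a 5 kHz cut-off of 1.044. All are absolute values, and none refers to baseline.

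Clinical intervention and follow-up schedules arm circumference and BIA at baseline and at eight postoperative times (1 week; 1, 3, 6, 12, 18, 24 and 36 months). Table 1, as reproduced, marks both measurements only from 1 week. The RVC subsection says that incidence is assessed at each follow-up time. It does not say whether the reported rate is per visit or cumulative. No confirmation or agreement between methods is required.

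The Introduction cites lymphoedema rates after sentinel lymph node biopsy (SLNB) of 4%, 7% and 8%. The last is specific in time: "lymphoedema was present in 8% of the patients 6 months after SLNB".

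**The concern.** A one-sided cut-off at mean + 2 SD is exceeded by about 2.3% of healthy readings. Here either of two readings suffices, volume is an additional route, and the assessment is repeated eight times. With an absolute cut-off, stable asymmetry present before surgery also registers as a new case. The two routes therefore differ in kind: RVC measures change, while SFBIA measures state.

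The trial has no concurrent SLNB arm in which the same false positives would occur. A reader can only set the reported rate beside published ones such as those in the Introduction. Reduced arm morbidity is the benefit the article expects patients to gain, and few true cases should occur when the axilla is not operated on. The specificity of the definition therefore matters more than usual, and the error works against the trial's own expectation.

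**Working it through.** The article states no expected BCRL rate or false-positive rate, so there is no figure of its own to reproduce.

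**Inputs from the article.** Cut-off at mean + 2 SD, exceeded upward; two frequencies per patient (four cut-offs are listed, but arm dominance selects two); baseline plus eight postoperative visits; cited SLNB rates of 4%, 7% and 8%; N = 311.

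**Assumptions, not in the article.** SFBIA ratios are normal; the healthy-women distribution applies to trial patients; true BCRL is zero; correlation between frequencies is 0.8 to 0.95; correlation between visits is equal for all pairs and 0.5 to 0.95.

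**Step 1, simple bounds.**
- One reading: 1 − Φ(2) = 0.0228.
- One visit, two readings: 2.3% if perfectly correlated; 1 − (1 − 0.02275)² = 4.5% if independent.
- Eight visits, one effective reading each: 2.3% if perfectly correlated; 1 − (1 − 0.02275)⁸ = 16.8% if independent.

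**Step 2, correlated readings.** Simulation of two frequencies at nine visits (400,000 patients), positive if z > 2 at either frequency. Each cell gives frequency correlation 0.8 / 0.95, as a percentage of all patients.

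| Between-visit correlation | Positive at a given visit | Ever positive, 8 visits | Given visit, baseline-negative | Ever, baseline-negative | Two consecutive visits, baseline-negative |
|---|---|---|---|---|---|
| 0.5 | 3.6 / 2.9 | 17.0 / 14.4 | 2.8 / 2.4 | 14.6 / 12.6 | 2.2 / 1.8 |
| 0.7 | 3.6 / 2.9 | 13.0 / 11.0 | 2.3 / 1.9 | 10.1 / 8.7 | 2.2 / 1.8 |
| 0.8 | 3.5 / 3.0 | 10.7 / 9.1 | 1.9 / 1.6 | 7.7 / 6.6 | 2.0 / 1.7 |
| 0.9 | 3.5 / 3.0 | 8.2 / 6.9 | 1.4 / 1.2 | 5.0 / 4.3 | 1.6 / 1.3 |
| 0.95 | 3.6 / 2.9 | 6.7 / 5.5 | 1.0 / 0.8 | 3.3 / 2.7 | 1.2 / 1.0 |

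**Step 3, in patients.** Of 311, 3% to 3.6% is about 9 to 11 false cases at a visit, and 5.5% to 17% is about 17 to 53 over eight visits. The cited 4%, 7% and 8% correspond to about 12, 22 and 25.

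**Step 4, the baseline part.** At correlations 0.9 (visits) and 0.95 (frequencies), 2.7 of the 6.9 percentage points were already positive before surgery: 2.7 / 6.9 = 39%. For RVC the baseline value is (A1 × U1)/(U1 × A1) − 1 = 0, so a baseline condition changes only the SFBIA route. RVC, as an alternative route, can only add to the figures above.

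**The case against.** **Per visit or cumulative.** A reader might infer that a positive at any of eight visits makes a case and that the trial will therefore report 7% or more from false positives alone. The article does not say this. Assessment at each follow-up time fits per-visit reporting equally well, and the per-visit rate of about 3% to 3.6% lies below all three cited SLNB rates. This stands.

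**Comparator.** The cited 8% is a 6-month figure, so its counterpart is the per-visit rate. The article does not give the measurement methods behind the three rates, and it sets no BCRL hypothesis or target. To say that the trial would miss a benefit it set out to demonstrate goes too far: its stated aim is oncological safety.

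**Number of cut-offs.** Four are listed, but two apply to any patient and they differ by 0.001. Repeated visits drive the cumulative inflation, not the number of cut-offs.

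**Correlation.** A very stable ratio gives less inflation. With one effective reading per visit, the cumulative rate falls below 4% once the between-visit correlation exceeds about 0.96.

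**A legitimate choice.** The cut-offs come from a cited source not available here, and favouring sensitivity for a morbidity endpoint is defensible. This argues against making two-visit confirmation the main definition, because late visits are 6 to 12 months apart.

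**Missing detail.** The full protocol might exclude baseline-positive women. However, the article states the diagnostic rule completely, and that rule contains no such condition. Followed as written, it counts pre-existing asymmetry on either reading of incidence, so the baseline point survives.

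**Conclusion.** The point holds in a limited form. The SFBIA route diagnoses incident BCRL from an absolute value, so asymmetry that preceded surgery is counted; this does not depend on the assumed correlations. Under the stated assumptions, false positives are about 3% to 3.6% per visit. They are about 5.5% to 17% if incidence is cumulative, which overlaps the cited 4% to 8%, but that reading is not fixed by the text.

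The effect is confined to a descriptive secondary endpoint. The primary endpoint and N = 311 do not depend on it. It should still be corrected, because without a control arm the reported rate has to stand alone.

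**What to change.** 1. Count incident BCRL only when the criterion was not met at baseline. False positives fall to about 1% to 3% per visit, or about 3% to 15% cumulative.
2. Report RVC-defined and SFBIA-defined BCRL separately, and label every rate as per-visit or cumulative. The labels matter because the baseline condition alone still leaves a wide cumulative range.
3. Add a supporting analysis: the rate confirmed at two consecutive scheduled visits in baseline-negative patients (about 1% to 2% false positive). Show a first positive at 36 months separately as unconfirmed.
4. Confirm that baseline BIA is collected, and reconcile Clinical intervention and follow-up with Table 1. Item 1 depends on it.

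The cost is endpoint wording and programming, provided the baseline measurement exists. The confirmed rate misses transient swelling and can lag by up to 12 months at late visits, which is why it is proposed as supporting only.

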### Sample size calculation

In this study, we used PASS software (version 2021) to perform a sample size calculation for a one-proportion non-inferiority test. The sample size was based on the primary endpoint of iDFS. According to the literature exploration and previous research results, it is expected that the 3 year iDFS in patients undergoing SLNB is about 90%. We set the non-inferiority margin at 5%, with a power of 80%, a significance level (α) of 0.05 and a 95% CI. Considering a 10% dropout rate, PASS software calculated the required sample size to be 311 patients.

### Data collection and management

This study uses an electronic case report form to manage and record the study data, and a password-protected access system will be set up to maintain participant confidentiality. The principal investigator has full responsibility of entire projects of this trial. The researchers needed to ensure that the data entry and correction were timely, complete, accurate and truthful. To ensure the accuracy of the data, double-entry and proofreading will be done independently by two data administrators. The clinical supervisor will perform data checking after the end of the study. The researcher will reply and follow-up on corrections promptly when the data are found to be incomplete inconsistent are challenged. If a subject withdraws their informed consent during participation in a clinical trial, no data will be collected after withdrawal. Study-related data collected before withdrawal will be retained and used for up to 3 years after withdrawal. At the end of the study, the principal investigator will submit a final report for review and written approval by the ethics committee.

### Statistical analysis

The primary analysis will use an intention-to-treat (ITT) analysis. For categorical variables, the χ2 test or Fisher’ s exact test will be used, and the data will be presented as totals, percentiles and frequencies. For continuous variables, descriptive statistics will be analysed using mean, SD or median and IQR. Independent samples t-tests will be used for normally distributed continuous variables, and nonparametric tests will be used for skewed data to analyse the results. Kaplan–Meier curves and log-rank tests will be used to determine the statistical significance of variables in the survival outcome categories (iDFS) and survival curves will be plotted. The prognostic significance of variables will be assessed using univariate and multivariate COX risk regression analyses. HR and 95% CI will be calculated. For each statistical analysis, a p value <0.05 will be considered statistically significant.

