## Methods and analysis

### Trial design and setting

This study is a prospective, noninferiority, single-arm, phase II open-label clinical trial conducted at the First Hospital of Nanjing Medical University. Patients with unilateral invasive breast cancer (tumor ≤3 cm) and assessed as cN0 will be eligible for inclusion. The enrolled patients are required to complete two or more imaging tests, including axillary ultrasound assessed as axillary lymph-node-negative, and other tests including MRI, PET-CT and [18F]-FDG PET/MRI. Patients with suspected lymph node metastasis will be directly excluded from enrollment. All patients are required to undergo preoperative coarse needle aspiration or intraoperative mass biopsy for pathologically confirmed invasive breast cancer (regardless of pathological type). Subsequently, surgeons will be required to provide a detailed explanation of the potential benefits and risks associated with the omission of SLNB to eligible patients. Before any surgical procedure is undertaken, patients must provide written informed consent. Following consent, patients will undergo BCS or mastectomy (allowing for breast reconstruction) without axillary surgery, with a postoperative follow-up of 3 years.

This clinical study will be conducted following the relevant provisions of the Declaration of Helsinki, and it was registered at http://www.clinicaltrials.gov (NCT number: NCT05935150). The study was reported according to the Standard Protocol Items: Recommendations for Interventional Trials (SPIRIT) checklist.^29^ The detailed flow chart of the study is shown in figure 1.

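### The Statistical analysis section does not carry forward the one-proportion non-inferiority test that sizes the trial, and its unpaired t-test does not suit FACT-B and Quick DASH change from baseline

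*Protocol article*

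**What the plan says.** Trial design and setting describes a "prospective, noninferiority, single-arm, phase II open-label clinical trial". There is no concurrent SLNB group.

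Sample size calculation reports that PASS was used to "perform a sample size calculation for a one-proportion non-inferiority test", based on iDFS. The reference is given as "it is expected that the 3 year iDFS in patients undergoing SLNB is about 90" per cent. The remaining inputs are "We set the non-inferiority margin at 5%, with a power of 80%, a significance level (α) of 0.05 and a 95% CI", and then "Considering a 10% dropout rate, PASS software calculated the required sample size to be 311 patients". The implied boundary is 90% − 5% = 85%. Neither 85% nor the sidedness of the test is written out.

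Statistical analysis gives the methods. For iDFS: "Kaplan–Meier curves and log-rank tests will be used to determine the statistical significance of variables in the survival outcome categories (iDFS"). Univariate and multivariate Cox models follow, for prognostic significance. For other continuous data: "Independent samples t-tests will be used for normally distributed continuous variables", with nonparametric tests if skewed. One threshold, p<0.05, applies to every analysis. The section contains no comparison of 3-year iDFS with a fixed value, no confidence-limit rule, and no paired or repeated-measures method.

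The secondary endpoints set the aim for the questionnaires: "The FACT-B scale will be used to assess changes in QoL in breast cancer patients with SLNB omission from baseline to 3 years after surgery". Quick DASH is described in the same way for arm morbidity. The article schedules both at baseline and at eight postoperative visits up to 36 months.

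**The concern.** The section that should say how the primary question is decided specifies analyses of a different question. In a single cohort, a log-rank p value or a hazard ratio compares patients with and without some characteristic. If two subgroups have the same iDFS, the log-rank test is null whether their common value lies above or below 85%. A reader following the section as written would finish with p values for prognostic factors and no non-inferiority conclusion. The Introduction makes a phase III trial depend on meeting the non-inferiority endpoint, so the rule for meeting it should be fixed before the data are seen.

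The second issue is smaller. FACT-B and Quick DASH are meant to show change over time in the same women. The only parametric test named for continuous data assumes two independent sets of people. Used for change from baseline, it ignores the within-patient correlation and is less able to detect worsening arm function or quality of life.

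**Working it through.** **1. Which test does 311 belong to?** Inputs from Sample size calculation: p1 = 0.90, p0 = 0.90 − 0.05 = 0.85, power 0.80, dropout 10%. The standard deviations are √(0.85 × 0.15) = 0.357 at p0 and √(0.90 × 0.10) = 0.300 at p1.

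- One-sided 0.05, null and alternative variances: n = [(1.645 × 0.357 + 0.842 × 0.300)/0.05]² = 282.1. Multiplying by 1.10 gives 310.3, rounded up to **311**. Dividing 283 by 0.90 gives 315.
- One-sided 0.025, variance at 90% only: n = [(1.960 + 0.842) × 0.300/0.05]² = 282.6. Multiplying by 1.10 gives 310.8, again **311**.
- One-sided 0.025, null and alternative variances: n = 363, or 404 after dividing by 0.90. This does not fit.

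So 311 is the size of a one-sample test against 85%. Two routes with different sidedness reach it, so the number does not reveal which was meant.

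**2. Design against analysis.**

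| Item | Sample size calculation | Statistical analysis |
|---|---|---|
| Question for iDFS | Is 3-year iDFS above 85%? | Which variables are associated with iDFS? |
| Method | One-proportion non-inferiority test | Log-rank, Cox |
| Decision | 5-point margin, alpha 0.05, 95% CI | p<0.05 for each analysis |

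The right-hand column does not contain the test in the left-hand column.

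**3. What the open sidedness is worth.** Exact binomial against 85% with true iDFS 90%, complete 3-year outcome assumed:

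| Patients | One-sided level | Event-free needed | Power |
|---|---|---|---|
| 311 | 5% | 275 | 85% |
| 311 | 2.5% | 277 | 74% |
| 280 (311 less 10%) | 5% | 249 | 76% |
| 280 (311 less 10%) | 2.5% | 250 | 70% |

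Kaplan–Meier keeps patients who drop out in the analysis until they leave. A simulation used 311 patients, exponential event times with 90% iDFS at 36 months, exponential dropout of 10% over 36 months (assumed), and a complementary log-log lower limit. Power was about **82%** at one-sided 5% and about **70%** at one-sided 2.5%. With true iDFS at 85%, the type I error was just under 5% and about 2.0%. Without dropout the powers were about 85% and 74–75%, in line with the exact binomial.

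**4. Unpaired test on paired data.** With equal variances σ² at two visits, n patients and correlation ρ:

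- Variance of the mean change: 2σ²(1 − ρ)/n. The unpaired test assumes 2σ²/n.
- Ratio of standard errors: 1/√(1 − ρ).
- True two-sided error of a nominal 0.05 test: 2[1 − Φ(1.96/√(1 − ρ))].
- Power when the paired test has 80%: Φ(2.80 − 1.96/√(1 − ρ)). The unpaired statistic has true variance 1 − ρ, and this formula allows for it.

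| ρ (assumed) | SE ratio | True error | Power |
|---|---|---|---|
| 0.3 | 1.20 | 0.019 | 68% |
| 0.5 | 1.41 | 0.0056 | 51% |
| 0.7 | 1.83 | 0.0003 | 22% |

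The article gives no correlation, so 0.3 to 0.7 is an illustrative range.

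**The case against.** Several stronger readings are tempting, and the document does not support them.

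- **That the tests need groups the trial lacks.** The log-rank and Cox sentences concern variables. The cohort has real subgroups, such as breast-conserving surgery versus mastectomy and receptor subtypes. As secondary prognostic analyses these tests are sound.
- **That non-inferiority is tested nowhere.** The sample size section names the right test, reference, margin and alpha, and ties them to iDFS. The intention can be recovered. What stands is that the analysis section does not take it up and names other methods in its place.
- **That this is detail for an analysis plan not shown.** This is fair for the choice of transformation, the form of a mixed model or exact intervals. It does not cover the mismatch, because the article does state methods for iDFS and they answer another question.
- **That the t-test is assigned to the questionnaires.** It is not, by name. It reaches FACT-B and Quick DASH only through the general rule, and a t-test of change scores between two subgroups would be valid. What stands is that the stated aim is change within patients and no suitable method is named for it.
- **That arm volume and lymphoedema share the fault.** Relative volume change is already expressed against each patient's own baseline. Nothing says that chi-square tests will compare lymphoedema between visits; incidence is simply assessed at each one.

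The t-test error is also conservative under positive correlation. It costs power on secondary endpoints and does not create false positive findings.

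**Conclusion.** The point holds as a mismatch between two sections. The trial is sized to test 3-year iDFS against 85%, but the analysis section gives only prognostic-factor methods for iDFS, and these cannot settle that question. The confidence level is also undetermined. It matters by about 12 points of power (82% against 70%), assuming true iDFS of 90%, 10% dropout and follow-up to 36 months for everyone else. At one-sided 5% the planned 311 is adequate. If the lower limit of a two-sided 95% CI is meant, the stated 80% power is not reached under the Kaplan–Meier analysis. The mismatch on the primary endpoint must be resolved before analysis.

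The questionnaire issue is secondary. It depends on the general t-test rule being applied to change from baseline, and its size depends on correlations that the article does not give.

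**What to change.** In Statistical analysis:

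1. State that the primary analysis is the Kaplan–Meier estimate of 36-month iDFS in the ITT set, and that non-inferiority is concluded if its lower confidence limit exceeds 85%.
2. State the confidence level and sidedness, and make Sample size calculation agree. If the limit is one-sided 95%, 311 can stand. If it is the lower limit of a two-sided 95% CI, restate the power (about 70% under the assumptions above) or revisit the sample size.
3. Label the log-rank and Cox analyses exploratory.
4. For change from baseline in FACT-B and Quick DASH, name paired tests or a repeated-measures mixed model. Keep independent-samples tests for comparisons between subgroups.

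The cost is rewriting one section and adding a sentence to another. No new data are needed, and no additional patients if one-sided 5% is intended.
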